## Abstract

**Background:**

Obesity is a global problem leading to reduced life expectancy, cardiovascular diseases, diabetes and many types of cancer. Even people willing to accept treatment only achieve a mean weight loss of about 5 kg using commercial weight loss programs. Surgical interventions, e.g. sleeve gastrectomy or gastric bypass are effective but accompanied by risk of serious complications and side effects. Less invasive endoscopic procedures mainly comprise the intragastric balloon (IB) and the duodenal-jejunal bypass liner (DJBL). To date, a randomized comparison between these devices has not been undertaken or shown to be superior to a sham procedure.

**Methods:**

We designed a multi-center, randomized, patient and assessor-blinded, controlled trial comparing weight loss in endoscopically implanted IB vs. DJBL vs. a sham procedure. A total of 150 patients with a BMI > 35 kg/m^2^ or > 30 with obesity-related comorbidities and indication for proton pump inhibitors are randomized to receive either IB, DJBL or a sham gastroscopy (2:2:1 ratio). All participants undergo regular dietary consultation. The IB will be removed after 6 months, whereas the DJBL will be explanted after 12 months. All patients will receive gastroscopies at implantation and explantation of the devices or sedation without gastroscopy to maintain blinding. Main exclusion criteria are malignant diseases, peptic ulcer or previous bariatric intervention. Weight loss 12 months after explantation of the devices, changes in comorbidities, quality of life, complication rates and safety will be evaluated.

**Discussion:**

This trial could help to identify the most effective and safest endoscopic device, thus determining the new standard procedure for endoscopic bariatric treatment.

**Trial registration:**

16th January 2017. DRKS00011036. Funded by the German Research Foundation (DFG).

## Background

Obesity is a growing global problem and an estimated 312 million people worldwide are affected [1]. Many studies have shown reduced life expectancy, higher risk of cardiovascular, pulmonary and gastrointestinal diseases, diabetes and many types of cancer to be associated with obesity [2]. Managing obesity is often disappointing as lifestyle alterations are an important, but frequently inadequate intervention. Although even moderate weight loss of 5–10% of body weight is associated with a meaningful improvement in insulin resistance, blood pressure and dyslipidemia [2, 3], only 20% of obese people are willing to accept treatment [1]. In addition, conservative treatment results only in mean weight loss of about 5 kg after one year using commercial weight loss programs and less than 2.5 kg using standard care. Moreover, only two thirds complete their respective programs even in the study setting [4].

Interventional surgical options comprise mostly sleeve gastrectomy and gastric bypass. These are effective but irreversible and associated with risk of serious perioperative complications, malabsorption and necessity of dietary supplementation. Furthermore, gastrointestinal symptoms such as reflux or vomiting occur in up to 20% of cases and in more than 10% of patients repeated surgery is required [5, 6]. Thus, many patients are unwilling to undergo this far-reaching step, and limited resources restrict surgical interventions to a small proportion of potential candidates.

In contrast, bariatric endoscopic procedures are reversible, minimally invasive, less costly and may offer a potentially lower risk approach compared to bariatric surgery [7]. These endoscopic approaches limit oral food intake, gastric exclusion or evoke malabsorption by partially inhibiting the breakdown or absorption of nutrients [8]. Intragastric balloons (IB) have been used for over 30 years and have been evaluated in many studies. They promote weight loss by physically decreasing intragastric volume and increasing gastric empting time. IB is usually removed after 6 months although recent devices allow implantation for up to 12 months [9]. Repeated implantations or implementation as an initial therapy prior to bariatric surgery are also feasible [10]. Serious side effects were very rare, with an incidence of migration and gastric perforation of 1.4 and 0.1%, respectively [11]. A large multicenter database analysis found a mean weight loss of 9.2 kg after 6 months and improvements of 5.1 kg after 3 years [12]. Nevertheless, in this analysis patients were included who had received additional therapy (lapband, gastric bypass or sleeve gastrectomy) after explantation of the balloons. In addition, many patients benefit from IB beyond explantation and relevant comorbidities such as arterial hypertension, diabetes or dyslipidemia were improved in about 50% of subjects [9, 13]. Nevertheless, although patients with IB reached a weight loss as high as 17.8 kg (> 10% of baseline) after 1 year in nonrandomized trials [14], some double-blinded, randomized, sham-controlled trials failed to show superiority of this device. Moreover, many patients did not achieve the goal of > 25% excess weight loss (EWL) or > 10% of baseline weight [15–17] and evidence of long-term effects is lacking [14]. Therefore, other endoscopic devices and strategies for the therapy of obesity have been developed.

The duodenal-jejunal bypass liner (DJBL) is an impermeable, fluoropolymer tube reversibly anchored to the duodenal bulb. Thereby, the chyme passes through the liner, while pancreatic and bile fluid passes outside the tube, resulting in an effective prevention of digestion and absorption in the upper intestine. The DJBL also has restrictive effects due to limited diameter of the sleeve and decelerated gastric emptying [18]. DJBL was originally developed for therapy of diabetes but is also known to induce considerable EWL of 19% [19] or 8.2 kg (EWL 11.9, 62% of participants achieved > 10% EWL) [20] up to 22.1 kg (EWL 47%) [21] after one year. In a six month follow-up after removal of the DJBL, some patients showed weight regain but continued to have a significantly higher weight loss compared to sham group [22]. Nevertheless, in analysis of both DJBL and IB, most studies evaluated excess weight loss (> 25% EWL) for definition of successful weight reduction. However, EWL strongly depends on baseline BMI and thus has unwanted properties [23, 24].

DJBL also improved glycemic control in obese patients with diabetes, and HbA1c was reduced from 8.7 ± 0.9% to 7.5 ± 1.6% [25]. These results were confirmed by several studies and a large meta-analysis [11, 18, 21, 26–29]. Furthermore, data indicating influence of DJBL on incretin hormone regulation and amelioration of fatty liver disease exist but remains preliminary [22, 26, 30, 31].

Although both devices were safe and showed mostly minor gastrointestinal complaints [7], a large multicenter study was dropped due to a high incidence of liver abscesses (3.5%) and an 11.7% rate of adverse events requiring removal of the DJBL (NCT01728116). In contrast, other studies did not observe such high rates of complications. In detail, serious adverse events in DJBL included migration (4.9%), GI bleeding (3.86%), sleeve obstruction (3.4%), liver abscess (0.126%), cholangitis (0.126%), acute cholecystitis (0.126%), and esophageal perforation (0.126%) secondary to trauma from an uncovered withdrawal [11].

In spite of convincing weight loss in patients undergoing endoscopic bariatric procedures, randomized studies comparing IB and DJBL are lacking. Thus, we designed a multi-center, randomized, controlled trial to compare weight loss in endoscopically implanted DJBL vs. IB vs. sham procedures. The weight-loss-endoscopy-trial (WET) aims to show the superiority of DJBL and IB compared with a sham group and to compare these devices. Additionally, the influence of DJBL and IB on diabetes and other comorbidities will be analyzed.

### Investigators

Patients will be recruited by the participating centers. All centers committed their participation in a covenant agreement with the trial coordinating institution. All investigators are experienced gastroenterologists and endoscopists and are certified as trial investigators who have attended additional courses on conducting trials according to the medical devices law.

### Data safety and monitoring board

An independent data safety and monitoring board consisting of three independent experts from the fields of gastroenterology, endocrinology and medical statistics will evaluate and supervise the clinical research data to assure patient safety and study integrity. The board will monitor the trial data, in particular the safety data and give their advice based on the periodical reviews.

### Medical device supply

The following medical devices will be used in this study. The EndoBarrier® system (endoscopically implanted DJBL, GI Dynamics, Duesseldorf, Germany, CE010311) and the Orbera Intragastric Balloon™ (Apollo Endosurgery, San Diego, USA, CE27493) are provided non-commercially by the study center. The DJBL will be implanted over a period of 12 months and the IB for a period of 6 months.

### On-site monitoring

On-site monitoring of the centers will be performed according to good clinical practice (ICH-GCP) guidelines. Personal visits will be carried out according to the SOPs of the Clinical Trial Center at Leipzig University. Clinical monitors will review entries into patient files (CRFs) on the basis of source documents (minimum of 30% source data verification). Monitors will verify source data and compliance with the procedures laid out in the trial protocol.

### Ethical considerations

The final study protocol was approved by the ethics committee of the Medical Faculty of the University of Leipzig (Trial registration number: DRKS00011036 on DRKS at 16th January 2017) in accordance with the declaration of Helsinki, the “Medical Association’s Professional Code of Conduct” and the principles of ICH-GCP guidelines (issued in June 1996, ISO14155 from 2012). In addition, the German Medical Devices Act (MPG, §§ 20-23a) was followed. Furthermore, local legal and regulatory authorities as well as the medical secrecy and the Federal Data Protection Act will be followed. All local ethics committees of the participating centers consented to the master ethics committee approval. Prior to enrollment, each patient will be given detailed information about the aims, scope and possible consequences of the trial by a physician. No diagnostic or interventional procedures required for the clinical trial will be performed without obtaining written consent from the patient.

### Study objectives

The primary objective of this study is to compare success rates (defined as ≥10% weight reduction from baseline weight) between the three procedures one year after removal. The primary analysis will use a generalized linear mixed model (GLMM) and a closed-testing procedure, meaning the three pairwise comparisons can be made without adjustment of the significance level if the global test is significant. Secondary aims include percentage weight loss at 12 months and success rates as well as percentage weight loss at 6 months and upon removal of the devices. In addition, complication rates and safety will be examined. Changes in obesity-related comorbidities (diabetes and associated diseases, hypertension, dyslipidemia, renal failure, coronary artery disease, heart failure, endocrinologic and psychiatric disorders, fatty liver and pulmonary diseases) and quality of life will also be assessed.

### Study design and setting

WET is a prospective, controlled, patient and assessor-blinded multi-center efficacy trial with two intervention arms and a sham procedure control arm. Patients will be randomized in a ratio of 2:2:1 to receive either IB, DJBL or sham procedure (gastroscopy with sedation). All enrolled patients will receive endoscopic procedures to implantat the devices or to maintain blinding. After 6 months, only the IB group, and after 12 months, only the DJBL group, will receive additional endoscopy to achieve explantation of the devices. The sham group will undergo sedation without gastroscopy at these same points in time. The duration of the trial for every patient is 24 months. The flowchart summarizing the trial visits is shown in Fig. 1.

**Fig. 1 Fig1:**
[figure not shown]
Treatment scheme

Each site is required to have an endoscopy unit which meets all German quality standards. The possibility to perform endoscopies under fluoroscopy is mandatory. All participating centers will perform endoscopies under conscious sedation or general anesthesia with qualified anesthetists. All sites will appoint blinded and unblinded investigators and all unblinded investigators are experienced endoscopists. They are trained in the implantation procedure of the DJBL device in pigs and have independently implanted at least 10 DJBLs and 10 IBs. The blinded investigator will attend the patient at all study visits and will be in charge of all patient contacts except the endoscopies, thus ensuring the assessor blinded nature of the study.

### Patients

In all participating sites, adult patients (≥ 18 years of age) with a BMI ≥ 35 kg/m^2^ or ≥ 30 kg/m^2^ and obesity related comorbidities, will be screened for eligibility for the trial. Obesity-related comorbidities comprise arterial hypertension, diabetes and associated diseases, cardiovascular diseases, dyslipidemia, arthrosis, obstructive sleep apnea as well as endocrinologic, psychiatric and gastrointestinal diseases.

Prior to enrollment, all participants attempted conservative weight-loss therapy that was ineffective. Furthermore, all patients must have a medical indication for the long term use of proton pump inhibitors (PPI), due to the fact that PPI are mandatory for the implantation of DJBLs and could affect the primary endpoint differently from placebo. Exclusion criteria for the study are listed in Table 1. Additionally, a gastroduodenoscopy has to be performed in all participants within three months before recruitment to exclude gastric or duodenal ulcer or a large hiatal hernia.

**Table 1 Tab1:** Exclusion criteria

Exclusion criteria	
Malignant disease	
Peptic ulcer	
Type 1 diabetes	
Large hiatus hernia	
Gastrointestinal diseases	
Previous gastric or bariatric surgery or endoscopic procedures (e.g. gastric balloon)	
High risk of gastrointestinal bleeding	
Symptomatic gallstones	
Contraindication for general anaesthesia	
Contraindication for devices according to the manufacturer	
Contraindication for proton pump inhibitors	
Non controlled gastrointestinal reflux disease	
Suspected lack of compliance	
Drug or alcohol abuse	
Pregnant or nursing women	
Fertile women without appropriate contraceptive measures while participating in the trial	
Participation in other interventional trials	
Psychological / mental or other inabilities to supply required information	

Regarding loss of follow up, compliance in the traditional sense is not an issue in this trial. The endoscopic devices cannot be explanted by the patient and any deviations from the recommended diet are part of the “real world” behavior that should be taken into account in the trial. On the other hand, problems with implantation and device failure take the place of compliance and are expected to be an issue. The failure estimates in the available literature vary wildly in the case of the DJBL from 0/16 (0%) over the course of one year [25] to 12/25 (48%) over the course of 12 weeks [20] and it was necessary to base our estimates of 15% for the DJBL and 10% for the IB on experience from our own university hospital. Loss to follow-up after removal is difficult to estimate because of the lack of data for long-term follow-up in comparable populations, yet we estimate a conservative 10%.

### Blinding and randomization

The study will be conducted in a patient and assessor-blinded fashion. Upon recruitment, each patient will receive a unique identification number to ensure both blinding of the patient and study team as well as identification after the end of the trial. Only the unblinded study team (implanters) will keep a personal list of patient numbers and names to match to patient records. After patients’ written informed consent has been obtained, the patient will be randomly assigned (1:2:2) either to the sham group (endoscopy in sedation) or one of the interventional groups (DJBL or IB), stratified with respect to diabetes status (yes/no) and center. The randomization will be performed electronically and every study participant can be identified by an ongoing unique randomization number. Randomization is organized and performed by the Center for Clinical Studies at the University of Leipzig and reported to the PI-center by fax within 24 h. The randomization codes are kept under lock and control, and they will be accessible 24 h a day in case of emergency code break.

### Statistical analysis

The primary end point for the trial is successful weight loss 12 months after removal. Successful weight loss is defined to be W_12month_/W_Baseline_ ≤ 0.9. The probability of successful weight loss per randomization arm, p_(success)_, is estimated to be the proportion of patients in that arm with successful weight loss. The null hypothesis of the trial is p_DBJL_(success) = p_IB_(success) = p_sham_(success). As mentioned above, primary and secondary study objectives will be analyzed by using a generalized linear mixed model (GLMM), which can take into account the longitudinal structure of the data as well as missing data. The stratification attribute diabetes will be included as a covariate in the model and a closed-testing procedure will be used. Thus, the three pair-wise tests will be performed if the global test is significant, where adjustment for the significance level is then unnecessary. Odds ratios and absolute differences in proportions along with confidence intervals based on the logistic regression will be presented. A sensitivity analysis will be performed in which the missing primary outcome will be treated as a failure, since dropping out is often rooted in poor weight loss. As a further sensitivity analysis, the 2 × 3 contingency table will be analyzed with a chi-squared test. A final sensitivity analysis will use the imputation results from the analysis of the continuous variable to define success/failure. Secondary analyses of weight as a continuous parameter will use a linear mixed model, but otherwise follow the lines of the primary analysis. As a sensitivity analysis, multiple imputation will be performed. Tests are all two-sided and the significance level is set at 5%.

The final analysis will be performed after the last patient has terminated the trial, and no interim analyses are planned.

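### Randomisation is stratified by diabetes and centre, but the stated models carry only diabetes; if centre is prognostic, the tests are slightly conservative and a little power is lost.

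*Protocol article*

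**What the plan says.** Under Blinding and randomization, the protocol article allocates patients "stratified with respect to diabetes status (yes/no) and center". Under Statistical analysis it fixes the adjustment: "The stratification attribute diabetes will be included as a covariate in the model and a closed-testing procedure will be used". The singular wording names one of the two factors. The mixed model is motivated as a "generalized linear mixed model (GLMM), which can take into account the longitudinal structure of the data as well as missing data"; clustering by centre is not given as a reason, and no random effects are described. The partial adjustment carries over to the continuous outcome: "Secondary analyses of weight as a continuous parameter will use a linear mixed model, but otherwise follow the lines of the primary analysis". The article gives no reason for leaving centre out.

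**The concern.** Stratifying by centre balances the arms within centres. Any between-centre variation in outcome then largely cancels from the treatment contrast. A model without centre still counts that variation as residual noise, so its standard errors no longer match the way patients were allocated.

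Centre effects are plausible here. The treatment includes repeated dietary consultation, and the article expects implantation problems and device failure to matter. It took its failure estimates from one hospital because the published DJBL rates run from 0% to 48%. At stake is a modest amount of power, least comfortably for DJBL versus IB on percentage weight loss, which is stated at 75%.

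**Working it through.** **Inputs from the article.** 150 patients at 2:2:1, so 60 DJBL, 60 IB and 30 sham; success rates 40%, 16% and 9%; two-sided 5% level; stated primary power 93% (global), 88% (DJBL versus sham) and 84% (DJBL versus IB); stated power for DJBL versus IB on percentage weight loss 75%, with a confidence interval width of 4.3 points.

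**Assumptions.** The article gives neither the number of centres nor any centre effect. I take 4 to 8 centres and a centre share of outcome variance, r, of 0 to 10%.

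**Step 1: reproduce the stated primary power without covariates.**
- Global: the overall rate is (24 + 9.6 + 2.7)/150 = 0.242. The noncentrality is [60(0.158)² + 60(0.082)² + 30(0.152)²]/(0.242 × 0.758) = 14.14. On 2 df this gives 93.1% (stated 93%).
- DJBL versus IB: (0.24 − 1.96 × 0.0820)/0.0790 = 1.00, giving 84.2% (stated 84%).
- DJBL versus sham: (0.31 − 1.96 × 0.1021)/0.0820 = 1.34, giving 91.0%; simulation under closed testing gives 89.8% (stated 88%).

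An analysis without covariates therefore comes close to the stated figures or exceeds them. They do not depend on adjusting for centre.

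**Step 2: continuous outcome, linear model.** If the model ignores a stratification factor with variance share r, the test statistic has true variance 1 − r rather than 1.
- Actual two-sided error = 2[1 − Φ(1.96/√(1 − r))]: 4.4% at r = 0.05 and 3.9% at r = 0.10.
- 75% power corresponds to a standardised effect of 1.96 + 0.6745 = 2.6345. With centre in the model, power = Φ(2.6345/√(1 − r) − 1.96): 77.1% at r = 0.05 and 79.3% at r = 0.10. That is 2 to 4 points above the stated 75%.
- Because the design already balances centres, the test without centre would itself have power Φ(0.6745/√(1 − r)): 75.6% and 76.1%. The net loss is then nearer 1.6 and 3.2 points, so 4 points is an outer figure.
- Cross-check: an SD of about 6, with failures and drop-outs mixed in, reproduces the stated width: 2 × 1.96 × 6 × √(2/60) = 4.29. With that SD, power for a 3-point difference (7.8 − 4.8) is 78.2%. Removing 5% of the variance gives 80.2%, and removing 10% gives 82.3%.

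**Step 3: binary primary endpoint, logistic model.** The √(1 − r) formula does not apply here, so trials were simulated: blocks of 5 within centre, marginal rates held at 40/16/9%, likelihood-ratio tests, closed testing, 800 to 2,000 trials per scenario. Power without and with centre as fixed effects, baseline weight having no effect:

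| Centres, r | Global | DJBL vs sham | DJBL vs IB |
|---|---|---|---|
| 6, 0% | 94.4 → 95.0 | 91.0 → 91.6 | 84.2 → 85.1 |
| 4, 5% | 93.2 → 93.8 | 90.0 → 91.4 | 84.2 → 84.8 |
| 8, 5% | 94.2 → 95.0 | 90.6 → 92.0 | 84.0 → 85.5 |
| 6, 10% | 94.6 → 95.4 | 90.5 → 92.3 | 84.0 → 86.2 |

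The largest gain from centre in any scenario was 2.7 points (DJBL versus sham, 92.1 → 94.8, with a strong baseline-weight effect also present). Monte Carlo error is about 0.5 to 1.3 points per figure, less for paired differences.

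Part of these gains is not genuine. With r = 0, fixed effects still appear to gain 0.6 to 0.9 points, and in null simulations they raised the global error to about 6 to 6.5%, against 4 to 5.5% without centre. The cause is sparse data: 30 × 9% = 2.7 expected sham successes. A random intercept was not simulated, so the table indicates the size of the gain rather than estimating it for the proposed model.

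**The case against.** The strongest reply is that the article is silent on centre and does not exclude it. It never says diabetes is the only term, it lists no random effects, and a centre intercept could sit in a full protocol or analysis plan that is not shown. That stands as a limit on how firmly one can say that centre will be ignored. It does not remove the point: the article does state its adjustment for the stratification, and that statement covers one factor of two. Followed as written, it leaves centre out.

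It is also fair that investigators must be trained and have implanted at least 10 of each device, which may narrow centre differences, and that the assumed variance share has no source in the article. Hence the range starts at zero.

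Three stronger readings are tempting, and the document does not support them:
- **That the precision is free.** Fixed centre effects disturb the type I error. In a logistic model, adjustment can raise power, but it does not shrink the standard error of the conditional log odds ratio, and it changes which odds ratio is estimated.
- **That the trial's main comparison stands at only 75%.** That figure belongs to the secondary continuous outcome; the primary DJBL versus IB comparison is stated at 84%.
- **That omitting baseline weight is an equal fault.** Weight is not a stratification factor, and it is already the denominator of the endpoint: "Successful weight loss is defined to be W_12month_/W_Baseline_ ≤ 0.9". Nothing in the article shows that it predicts percentage loss. If it does not, adding it changed simulated power by only −0.8 to +0.5 points.

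**Conclusion.** The point holds, and it is modest. The stated models include one of the two stratification factors. With centre explaining 0 to 10% of outcome variance, omitting it costs about 0 to 3 points of power on the primary endpoint and about 0 to 4 points for DJBL versus IB on percentage weight loss. On the continuous outcome, the actual error of a nominal 5% test falls to 4.4% at a 5% share and 3.9% at a 10% share. The direction is conservative, so no false-positive risk follows, and neither the sample size nor any stated power figure is undermined. The size rests wholly on the assumed centre variance and number of centres; if centre does not predict outcome, the loss is nil.

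**What to change.** State that centre enters both the primary generalized linear mixed model and the secondary linear mixed model as a random intercept beside diabetes, with a rule for pooling small centres if needed. Do not use fixed centre effects, given the sparse sham successes. If centre is left out on purpose, say why.

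The cost is a sentence or two and no new data. There are downsides: slightly more model complexity, possible convergence problems with few events (so name a fallback in advance), and an odds ratio that becomes conditional on centre. The absolute differences in proportions, which the article already promises, can be standardised over centre. Baseline weight may be added as an optional covariate, useful mainly if weight in kilograms is modelled; the text should then say which continuous measure is analysed.
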